## **12.9. EXPLORATORY ANALYSIS**

In addition a number of exploratory analyses will be conducted. No formal statistical hypothesis tests will be conducted. Predictors of survival will be assessed using Cox proportional hazards regression utilizing univariate and multivariate models to assess association of selected parameters with the primary outcome. Some parameters to be assessed may include gender, age, race/ethnicity, presence of co-morbidities, type of CRRT modality, SOFA score and RIFLE predicted outcomes. Additional regression models may include interaction terms for the selected parameters to assess for evidence of a differential treatment effect. Other exploratory analyses on additional outcome measures will describe the following outcomes in the two randomized groups: infection as defined in Appendix D, pressor free days, recovery of renal function, SCD integrity, ICU LOS, Hospital LOS, duration of Renal Support, CRRT circuit life analysis and fluid removal analysis. Continuous outcomes will be summarized with sample size, mean, median, standard deviation, minimum, maximum and 95% confidence intervals; categorical outcomes will be presented with the counts and percents of subjects in each category along with 95% confidence limits. Additional, non pre-specified exploratory analyses may also be conducted.

## **13. ECONOMIC AND QUALITY OF LIFE (QOL) EVALUATION**

### **13.1. QOL AND ECONOMIC STUDY OBJECTIVES**

The specific objectives for the QOL and economic study are as follows:

- To assess health-related quality of life and health state utility between study groups 60 days after randomization.
- To estimate the costs of the hospital admissions in which renal replacement therapy is initiated and compare between groups.
- To measure major health care resource utilization from randomization to 60 days and compare between groups.
- To estimate total health care costs at 60 days and compare between groups.
- To estimate long-term cost effectiveness of renal replacement therapy for acute kidney injury using the SCD, relative to providing renal therapy without the SCD.

#### **14. DATA COLLECTION – STUDY MONITORING AND AUDIT**

The Principal Investigator is responsible for assuring the accuracy and completeness of all study documentation. Monitoring will be conducted within ICH/GCP Guidelines and CytoPherx, Inc. Clinical Monitoring Plan to ensure the following:

- The facilities continue to be acceptable.
- The protocol is appropriately followed.
- Any agreed upon changes to the protocol have been approved by the IRB and approval has been received in writing by CytoPherx, Inc.
- Accurate, complete and current records are maintained and available for all patients.
- For each subject, collection of protocol-required data and entry of that data into the CRFs must be completed as soon as reasonably possible and shall not be more than 90 days following that subject's last day in the study without permission from CytoPherx, Inc.
- The information recorded and submitted to CytoPherx, Inc. is representative of the patient's record and other supporting documentation.
- Accurate, complete and timely adverse event reports for serious adverse events are submitted to CytoPherx, Inc.
- The Principal Investigator continues to assume primary responsibility for the study.

The Investigator or designee must, upon request, provide to the Clinical Research Associate (CRA), Quality Assurance Auditor, or FDA Investigator the necessary study records for a thorough review of the study's progress. These records include, but are not limited to, original documents and records, such as hospital and clinic charts, consent forms, and laboratory records. The Principal Investigator is required to notify the Sponsor immediately of the following:

- Withdrawal of IRB Approval
- Any deviations from the protocol
- Notification that Informed Consent was not obtained or consent was withdrawn
- Any other instance in which the Investigator or Sponsor deems it necessary

## 17. APPENDICES

**APPENDIX A**  
**SEQUENTIAL ORGAN FAILURE SCORING SYSTEM (SOFA)** 

| ORGAN SYSTEM           | MEASURE                                    |
|------------------------|--------------------------------------------|
| Respiration            | PaO 2 to FiO 2 Ratio |
| Coagulation            | Platelet Count                             |
| Liver                  | Serum Bilirubin                            |
| Cardiovascular         | Hypotension                                |
| Central nervous system | Glasgow Coma Score                         |
| Renal                  | Serum Creatinine or Urine Output           |

| MEASURE                                                                                                                      | FINDING                                                    | POINTS |
|------------------------------------------------------------------------------------------------------------------------------|------------------------------------------------------------|--------|
| PaO 2 to FiO 2 Ratio
(please see
Pulmonary System
Conversion Table for
Non-ventilated Pts) | ≥ 400 mmHg                                                 | 0      |
|                                                                                                                              | 300 – 399 mmHg                                             | 1      |
|                                                                                                                              | 200 – 299 mmHg                                             | 2      |
|                                                                                                                              | 100 – 199 mmHg                                             | 3      |
|                                                                                                                              | < 100 mmHg                                                 | 4      |
| Platelet Count                                                                                                               | ≥150 x 10  /mm                     | 0      |
|                                                                                                                              | 100 – 149 x 10  /mm                | 1      |
|                                                                                                                              | 50 – 99 x 10  /mm                  | 2      |
|                                                                                                                              | 20 – 49 x 10  /mm                  | 3      |
|                                                                                                                              | < 20 x 10  /mm                     | 4      |
| Serum Bilirubin                                                                                                              | < 1.2 mg/dL                                                | 0      |
|                                                                                                                              | 1.2 – 1.9 mg/dL                                            | 1      |
|                                                                                                                              | 2.0 – 5.9 mg/dL                                            | 2      |
|                                                                                                                              | 6.0 – 11.9 mg/dL                                           | 3      |
|                                                                                                                              | ≥12.0 mg/dL                                                | 4      |
| Hypotension                                                                                                                  | Mean arterial pressure ≥70 mmHg                            | 0      |
|                                                                                                                              | Mean arterial pressure < 70 mmHg no
pressor agents used | 1      |
|                                                                                                                              | Dobutamine any dose                                        | 2      |
|                                                                                                                              | Dopamine ≤ 5 µg per kg per min                             | 2      |
|                                                                                                                              | Dopamine > 5 – 15 µg per kg per min                        | 3      |
|                                                                                                                              | Dopamine > 15 µg per kg per min                            | 4      |
|                                                                                                                              | Epinephrine ≤ 0.1 µg per kg per min                        | 3      |
|                                                                                                                              | Epinephrine > 0.1 µg per kg per min                        | 4      |
|                                                                                                                              | Norepinephrine ≤ 0.1 µg per kg per min                     | 3      |
|                                                                                                                              | Norepinephrine > 0.1 µg per kg per min                     | 4      |

**SEQUENTIAL ORGAN FAILURE SCORING SYSTEM (SOFA)**  
(Continued)

| MEASURE                             | FINDING                           | POINTS |
|-------------------------------------|-----------------------------------|--------|
| Glasgow Coma Score                  | 15                                | 0      |
|                                     | 13 – 14                           | 1      |
|                                     | 10 – 12                           | 2      |
|                                     | 6 – 9                             | 3      |
|                                     | 3 – 5                             | 4      |
| Serum Creatinine or
Urine Output | Serum Creatinine < 1.2 mg/dL      | 0      |
|                                     | Serum Creatinine 1.2 – 1.9 mg/dL  | 1      |
|                                     | Serum Creatinine 2.0 – 3.4 mg/dL  | 2      |
|                                     | Serum Creatinine 3.5 – 4.9 mg/dL  | 3      |
|                                     | Serum Creatinine > 5.0 mg/dL      | 4      |
|                                     | Urine Output 200 – 499 mL per day | 3      |
|                                     | Urine Output < 200 mL per day     | 4      |

Conventions used for the above table include:

- PaO2 is in mmHg and FiO2 in percent from 0.21 to 1.00.
- Adrenergic agents as administered for at least 1 hour with doses in µg per kg per min.
- A score of 0 indicates normal and a score of 4 indicates most abnormal.
- Data can be collected and the score calculated daily during the course of the admission.
- Mean systemic arterial pressure = systolic arterial pressure + twice the diastolic arterial pressure divided by 3. All values should be in mmHg.
- Total Modified SOFA score = SUM (points for all 6 measures)

## SEQUENTIAL ORGAN FAILURE SCORING SYSTEM (SOFA)

(Continued)

### Interpretation:

1. Minimum total score: 0
2. Maximum total score: 24
3. The higher the organ scores the greater the organ dysfunction.
4. The higher the total scores the greater the multi-organ dysfunction.

|                     | MORTALITY RATE BY MODIFIED SOFA SCORE |          |          |          |          |
|---------------------|----------------------------------------------|----------|----------|----------|----------|
| ORGAN SYSTEM | 0                                     | 1 | 2 | 3 | 4 |
| Respiratory         | 20%                                          | 27%      | 32%      | 46%      | 64%      |
| Cardiovascular      | 22%                                          | 32%      | 55%      | 55%      | 55%      |
| Coagulation         | 35%                                          | 35%      | 35%      | 64%      | 64%      |
| CNS                 | 26%                                          | 35%      | 46%      | 56%      | 70%      |
| Liver               | 32%                                          | 34%      | 50%      | 53%      | 56%      |
| Renal               | 25%                                          | 40%      | 46%      | 56%      | 64%      |

### **GLASGOW COMA SCORE**

The Glasgow Coma Score (GCS) is scored between 3 and 15, 3 being the worst and 15 the best. It is composed of the three parameters listed below:

#### **Best Eye Response (4)**

1. No eye opening
2. Eye opening to pain
3. Eye opening to verbal command
4. Eyes open spontaneously

#### **Best Verbal Response (5)**

1. No verbal response
2. Incomprehensible sounds
3. Inappropriate words
4. Confused
5. Oriented

#### **Best Motor Response (6)**

1. No motor response
2. Extension to pain
3. Flexion to pain
4. Withdrawal from pain
5. Localizing pain
6. Obeys commands

A Coma Score of 13 or higher correlates with a mild brain injury, 9 to 12 is a moderate injury and 8 or less a severe brain injury.

## SEQUENTIAL ORGAN FAILURE SCORING SYSTEM (SOFA)

(Continued)

### PULMONARY SYSTEM CONVERSION TABLE

| O2 Saturation Conversion Table                                                                                     |  | Conversion Table for FiO2 |
|--------------------------------------------------------------------------------------------------------------------------------------|--|---------------------------------------------|
| Pulse oximetry O 2 saturation may be used for calculating PaO 2 /FiO 2 ratio when ABG not available |  | When measured on mask or nasal cannula      |

| SaO 2 (%) | Calculated PaO 2 |
|----------------------|-----------------------------|
| 80                   | 44                          |
| 81                   | 45                          |
| 82                   | 46                          |
| 83                   | 47                          |
| 84                   | 49                          |
| 85                   | 50                          |
| 86                   | 52                          |
| 87                   | 53                          |
| 88                   | 55                          |
| 89                   | 57                          |
| 90                   | 60                          |
| 91                   | 62                          |
| 92                   | 65                          |
| 93                   | 69                          |
| 94                   | 73                          |
| 95                   | 79                          |
| 96                   | 86                          |
| 97                   | 96                          |
| 98                   | 112                         |
| 99                   | 145                         |
|                      |                             |

| Nasal Cannula                         |                      |
|---------------------------------------|----------------------|
| 100% O 2 Flow Rate (L/min) | FiO 2 (%) |
| 1                                     | 24                   |
| 2                                     | 28                   |
| 3                                     | 32                   |
| 4                                     | 36                   |
| 5                                     | 40                   |
| 6                                     | 44                   |
|                                       |                      |
| Oxygen Mask                           |                      |
| 100% O 2 Flow Rate (L/min) | FiO 2 (%) |
| 5-6                                   | 40                   |
| 6-7                                   | 50                   |
| 7-8                                   | 60                   |
| 9                                     | 90                   |
| 10                                    | 99+                  |
|                                       |                      |
| Mask with Reservoir Bag               |                      |
| 100% O 2 Flow Rate (L/min) | FiO 2 (%) |
| 6                                     | 60                   |
| 7                                     | 70                   |
| 8                                     | 80                   |

## APPENDIX B

### DEFINITIONS OF ACUTE KIDNEY INJURY/ACUTE TUBULAR NECROSIS

#### Acute Kidney Injury/Acute Tubular Necrosis

Acute Kidney Injury (AKI) is sudden loss of the ability of the kidneys to excrete wastes, concentrate urine, and conserve electrolytes.

Acute tubular necrosis (ATN) is defined in this protocol as AKI due to hemodynamic or toxic etiologies. These conditions are found in circumstances of acute ischemic or nephrotoxic injury and conform to the following criteria:

**Oliguria: average < 20 mL/hour for > 6–12 hours      OR**

**Serum Creatinine:  $\geq$  to an increase of 2 mg/dL for males over a period of  $\leq$  4 days or  $\geq$  to an increase of 1.5 mg/dL in females over a period of  $\leq$  4 days**

**(Note: pre-renal, hepatorenal, vascular, interstitial, glomerular, and obstructive etiologies are excluded on clinical or other diagnostic grounds.)**

ATN develops predominantly due to the injury and necrosis of HPTC (Human Proximal Tubular Cells). ATN is caused by ischemia of the kidneys or by exposure to nephrotoxic agents. Risks for ATN include injury or trauma with resulting damage to the muscles, recent major surgery, blood transfusion reaction, septic shock or other forms of shock, and severe hypotension longer than 30 minutes.

Any condition that causes a reduction in the amount of blood being pumped by the heart may cause ATN. Liver disease and damage caused by diabetes mellitus (diabetic nephropathy) may predispose a person to the condition. ATN can also be caused by exposure to nephrotoxic agents (e.g., aminoglycoside antibiotics), antifungal agents (e.g., amphotericin), medications to prevent rejection of transplanted organs (e.g., cyclosporine), dye used for radiographic studies, and other toxins. In SCD studies, only patients with ATN due to hemodynamic or toxic etiologies are eligible for study participation. As noted above, pre-renal, hepatorenal, vascular, interstitial glomerular and obstructive etiologies are excluded on clinical or other diagnostic grounds.

## APPENDIX C

### DEFINITIONS OF SEPSIS AND SEVERE SEPSIS 

#### A. SEPSIS

Sepsis is defined in this protocol as a condition which has clinical evidence suggestive of infection, plus signs of a systemic response to infection with all of the following:

|                          |                                        |
|--------------------------|----------------------------------------|
| Tachypnea         | > 20 breaths/min |
| Tachycardia       | > 90 beats/min               |
| Hyper/Hypothermia | > 38.4°C or < 35.6°C      |

 If the patient is mechanically ventilated, > 10L/min.

#### B. SEVERE SEPSIS

Severe Sepsis is defined in this protocol as SEPSIS with one or more signs of organ dysfunction, such as:

|                                                    |                                                                                                                   |
|----------------------------------------------------|-------------------------------------------------------------------------------------------------------------------|
| Metabolic acidosis                          | Higher than upper limit                                                                                    |
| Acute encephalopathy                        |                                                                                                                   |
| Oliguria                                    | <0.5 ml/kg for at least one (1) hour                                                                    |
| Hypoxemia or DIC or hypotension | PaO2/fiO2 <280^3
<90 mmHg (or a 40 mmHg decrease below baseline) |

 Disseminated intravascular coagulation

 If the patient is mechanically ventilated, >10L/min

## **APPENDIX D DEFINITIONS**

### **RENAL REPLACEMENT THERAPY (RRT) DEPENDANCY AT DAY 60**

RRT dependency at day 60 is defined as patient not receiving any form of intermittent or continuous renal replacement therapy at 60 days post enrollment in the study with no plans for additional intermittent or continuous renal replacement therapy.

### **NUMBER OF VENTILATOR FREE DAYS (VFD) AT DAY 28**

Ventilator Free Days (VFD) to day 28 is defined as the number of days of unassisted breathing to day 28 after randomization, assuming a patient survives for at least two consecutive calendar days after initiating unassisted breathing and remains free of assisted breathing. If a patient returns to assisted breathing and subsequently achieves unassisted breathing prior to day 28, VFD will be counted from the end of the last period of assisted breathing to day 28 unless a period of assisted breathing was less than 24 hours and the purpose of assisted breathing was a surgical procedure. If the patient is receiving assisted ventilation at day 28 or dies prior to day 28, VFD will be zero (0).

Unassisted breathing is defined as breathing with a face mask or nasal prong oxygen (or room air) following extubation, T-tube breathing, breathing with continuous positive pressure (CPAP  $\leq 5$  cm H2O), or tracheotomy mask breathing.

### **VASOPRESSOR USAGE**

Vasopressor usage will be determined by:

1. Length of vasopressor treatment until day 28 or ICU discharge whichever comes first.
2. Time on more than a single vasopressor until day 28 or ICU discharge whichever comes first.

### **INFECTION:**

Infection will be defined as "a positive body fluid (blood, sputum, urine, etc.), tissue (muscle, skin, etc.), or indwelling device (catheter tip, pacer lead, etc.) culture from non-contaminant pathogen." Infection rate is the total number of infection episodes up to hospital discharge or day 60 (whichever comes sooner) per group.

### **HOSPITAL LENGTH OF STAY:**

Both ICU and Hospital length of stay will be defined based on the ICU and acute hospital admissions during which the patient was randomized and enrolled in the SCD003 Trial. Length of stay will be evaluated on the basis of the mean number of days of ICU/hospital stay following randomization into the SCD003 trial. Hospital discharge will be defined as discharge from acute care, whether to acute rehabilitation, transitional care, long term care or home.

### **DURATION OF RENAL SUPPORT:**

The duration of renal support will be defined as the numbers of days from the initiation of renal replacement therapy to final dialysis treatment. Duration of renal support will be censored if the patient is still dialysis dependant at the time of death.

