### 1.1. RATIONALE FOR THERAPY

Our primary hypothesis is that up to seven sequential 24-hour SCD treatments will improve survival in patients with Acute Kidney Injury (AKI) as compared to CRRT alone (standard of care). Further, SCD therapy may reduce the duration of maintenance dialysis secondary to AKI due to acute tubular necrosis (ATN). ATN is an acute reversible process and if not reversed in three months, it may not be reversed at all. [1, 2] Studies suggest that approximately 10% of AKI patients do not recover renal function [3, 4] and, therefore, require chronic dialysis.

Importantly, acute kidney injury is a highly lethal condition in critically ill patients. Despite improvements in acute medical care and advances in dialysis therapies, the mortality rate during the past four decades of this condition has not improved. Critically ill patients with AKI in hospital ICU settings have mortality rates of 50 to 80%. [5 - 9]

AKI promotes a systemic inflammatory response syndrome (SIRS) which results in systemic microvascular damage and, if severe, multi-organ dysfunction. [10,

11] Activated circulating leukocytes play a central role in this process. [12] Leukocytes, especially neutrophils, are major contributors to the pathogenesis and progression of many inflammatory disorders, including SIRS, sepsis, ischemia reperfusion injury, and acute respiratory distress syndrome (ARDS). Many therapeutic approaches are under investigation to limit the activation and tissue accumulation of leukocytes at sites of inflammation to minimize tissue destruction and disease progression. [13-15]

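### Duration of renal support is censored at death, and mean length of stay has no rule for deaths, so neither exploratory outcome can be read cleanly when planned mortality is 50% versus 35% (minor)

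*Protocol*

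**What the plan says.** Appendix D of the protocol gives the duration of renal support as "defined as the numbers of days from the initiation of renal replacement therapy to final dialysis treatment", and adds: "Duration of renal support will be censored if the patient is still dialysis dependant at the time of death".

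For ICU and hospital stay, Appendix D says: "Length of stay will be evaluated on the basis of the mean number of days of ICU/hospital stay following randomization". It also says what ends a hospital stay: "Hospital discharge will be defined as discharge from acute care, whether to acute rehabilitation, transitional care, long term care or home". Death is not among the ways a stay can end, and no rule is given for patients who die in hospital.

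Section 12.9 lists both among the exploratory outcomes to be described in the two randomized groups ("ICU LOS, Hospital LOS, duration of Renal Support, CRRT circuit life analysis and fluid removal analysis"). It sets the summary, "Continuous outcomes will be summarized with sample size, mean, median, standard deviation, minimum, maximum and 95% confidence intervals", and limits the inference: "No formal statistical hypothesis tests will be conducted".

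Two other definitions in Appendix D do give death a place. Ventilator-free days are zero for a patient who dies before day 28. A patient who is dialysis dependent at death is classed as having no renal recovery.

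**The concern.** Censoring assumes that a patient who leaves observation could still have the event later. A patient who died on dialysis cannot come off it. If few patients died, this would hardly matter, but section 12.2 plans for half the control arm and about a third of the device arm to die within 60 days.

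Three difficulties follow.

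- A duration defined as censored does not fit the summary in section 12.9. A mean and standard deviation of the recorded days would take each death on dialysis as a completed duration, which the censoring rule says it is not.
- A curve that respects the censoring estimates what would happen if nobody died. It cannot be read as the share of patients who come off dialysis.
- The same patient is a definite non-recovery under the renal recovery definition, but a possible later recovery under the duration definition.

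Length of stay has a related ambiguity. If death ends the stay, better survival lengthens the mean. If only discharged patients are averaged, the comparison is conditioned on something that happens after randomization.

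What is at stake is interpretation. Section 1.1 offers as part of the rationale that "SCD therapy may reduce the duration of maintenance dialysis secondary to AKI", so readers will look at the duration of renal support for support of that idea.

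**Working it through.** **Inputs from the protocol (section 12.2).** Death hazards are 0.01155 per day (CRRT alone) and 0.00718 per day (CRRT + SCD). They reproduce the planned mortality: 1 − exp(−60 × 0.01155) = 0.500 and 1 − exp(−60 × 0.00718) = 0.350. The protocol states no figure for duration of renal support or length of stay in this trial, so there is nothing further to reproduce.

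**Assumption.** The hazard g of coming off dialysis is constant, equal in both arms and independent of death, so the device changes survival only. The protocol gives no value; g = 0.02, 0.03 and 0.05 per day are shown.

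**Formulas**, with death hazard λ:

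- Curve censored at death, day 60: 1 − exp(−60g)
- Actually off dialysis alive by day 60 (death competing): g/(λ+g) × [1 − exp(−60(λ+g))]

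**Worked case, g = 0.03**

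- Censored curve, both arms: 1 − exp(−1.8) = 83.5%
- Control: 0.03/0.04155 × [1 − exp(−2.493)] = 0.7220 × 0.9173 = 66.2%
- SCD: 0.03/0.03718 × [1 − exp(−2.2308)] = 0.8069 × 0.8926 = 72.0%

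**Range**

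| g per day | Censored curve, both arms | Off alive, control | Off alive, SCD |
|---|---|---|---|
| 0.02 | 69.9% | 53.8% | 59.2% |
| 0.03 | 83.5% | 66.2% | 72.0% |
| 0.05 | 95.0% | 79.2% | 84.6% |

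The censored curve overstates the proportion coming off by about 16 to 17 points in the control arm and 10 to 11 points in the SCD arm.

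**Plain mean of days on dialysis.** If death is taken as the end, the mean through day 60 is [1 − exp(−60(λ+g))]/(λ+g). Control versus SCD, this gives 26.9 vs 29.6 (g = 0.02), 22.1 vs 24.0 (0.03) and 15.8 vs 16.9 (0.05). The SCD mean is 1.1 to 2.7 days longer with no effect on recovery at all.

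**Check with a different model.** A simulation of 400,000 patients per arm fixed mortality at 50% and 35% and let the device change only the time of death. Stays were lognormal with the pilot values in section 2.4.2 (ICU 15.0, SD 9.1; hospital 21.8, SD 10.9). Days on dialysis if alive were assumed lognormal (mean 15, SD 12). Death hazards were constant or front-loaded, and the correlation of severity with death was 0, +0.4 or −0.3.

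| Measure | SCD minus control, days |
|---|---|
| Hospital stay, death ends the stay | +0.8 to +1.9 |
| ICU stay, death ends the stay | +0.4 to +1.2 |
| Hospital stay, survivors only, independent | 0.0 |
| Hospital stay, survivors only, sicker patients die first | +0.8 to +0.9 |
| Hospital stay, survivors only, reverse association | −0.7 |
| Median days on dialysis, censored at death, independent | 0.0 |
| Same, sicker patients die first | +0.2 to +0.3 |
| Same, reverse association | −0.1 to −0.3 |

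When death ends the stay, the direction follows by logic: a patient whose death is postponed cannot have a shorter stay than before. For the other two measures the sign depends on an association the trial does not control.

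**The case against.** The strongest objections are these.

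**The censored comparison is not biased.** A reader might infer that censoring at death makes a life-saving device look worse. The calculation does not show that. For a device that changes only mortality, equal curves are the correct cause-specific answer. What stands is that the curve must not be read as the proportion coming off dialysis, and that a plain mean does not respect the censoring.

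**The protocol does not say that a death counts as a short stay.** This is correct. The pilot table in section 2.4.2 points the other way: its stays rest on 23 and 22 patients, exactly the numbers discharged from ICU and hospital by day 60. The rule for deaths may also sit in an analysis plan that is not shown. The length-of-stay part is therefore an ambiguity, not an error.

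**Section 12.9 does not expressly say that censored times will be averaged, and it also reports medians.** True, but the section makes no exception for this outcome, and an ordinary median of recorded days has the same difficulty with deaths.

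**The recovery hazards are pessimistic.** Hazards of 0.02 and 0.03 leave 30% and 16.5% still on dialysis at day 60 if nobody died. The pilot saw recovery in 24 of 24 survivors, and section 1.1 cites about 10% non-recovery. A hazard of 0.05 leaves 5%, and the gap between the censored and actual proportions is still 15.8 and 10.4 points.

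**Scoring death as zero free days also mixes survival with recovery.** This stands. In the simulation the mortality-only device gains 6.8 to 6.9 dialysis-free days and 5.7 to 5.9 hospital-free days. Such scores are a choice of estimand, not a correction.

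**The rationale has other measures.** Dialysis dependency at day 60 is a named secondary endpoint, and renal recovery is described separately.

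**Conclusion.** The point holds as a minor one. The protocol fixes censoring at death for an outcome where death is frequent and planned to differ by arm, pairs it with summaries unsuited to a censored duration, and treats the same patients as non-recoveries elsewhere in Appendix D. In the illustration the censored curve overstates coming off dialysis by roughly 10 to 17 points and does not show the 5 to 6 point difference in patients who actually come off alive. Those sizes rest on assumed constant hazards that are equal between arms and independent of death; only the mortality rates come from the protocol.

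For length of stay, the protocol leaves open which of two readings applies, and each has a known problem.

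Three stronger readings are not supported. The outcomes do not always lean against the device, since the sign can reverse. The protocol does not state that mean stay feeds the cost comparison; section 12.6 defers health economics to a separate plan. And no confirmatory result is touched, because both outcomes are exploratory and untested.

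**What to change.** In Appendix D and section 12.9:

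1. Replace censoring at death with death as a competing event. Describe, by arm, the cumulative incidence through day 60 of coming off renal replacement therapy alive, of ICU discharge alive and of hospital discharge alive.
2. State how in-hospital deaths enter length of stay. Keep mean stay as a description of resource use, shown separately for survivors and decedents.
3. If dialysis-free or hospital-free days with death scored zero are added, label them as composites of survival and recovery. They are optional.

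The cost is a few sentences and a few extra descriptive analyses. Dialysis status, discharge dates and deaths are already collected, and the current duration definition already needs the date of the last dialysis treatment. Nothing changes in the primary or secondary endpoints, alpha or sample size.
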